## Abstract

**Background::**

In the treatment of diabetes mellitus, the challenge is to integrate adequate
self-management into clinical care. Customization including goal setting,
monitoring, and feedback could be achieved through digitization. Digital
linking between different devices could simplify and promote
self-management. The aim of this study is to evaluate the outcome of
diabetes treatment assisted by a digital health application compared with
standard diabetes therapy.

**Methods::**

The DAVOS study is a 6-month-period prospective, multicentric, randomized
controlled trial. In total, 154 diabetes patients (age ≥18; treated with
insulin) will be recruited and randomized into control group or intervention
group. Both groups will receive standard diabetes care. The intervention
group will additionally use a diabetes app. HbA1c value will be monitored on
three separate defined visits. Primary endpoint is the overall reduction of
HbA1c value. Secondary endpoints (eg, usability of the app) will be
determined through patient-reported outcome questionnaires.

**Discussion::**

Through enhanced interaction of health care professionals, providers of the
app, and patients, the study aims to demonstrate improvement in the
self-management of diabetes. As part of the closure management, all patients
will be invited to use the examined application after completion of the
study. The DAVOS study will be conducted in accordance with the valid
version of the present study protocol and the internationally recognized
International Conference on Harmonization–Good Clinical Practice (ICH-GCP)
Guidelines. Special attention will be paid to European, national, and
regional requirements for the approval, provision, and use of medical
devices. The study was registered in the German Register of Clinical Trials
(DRKS) with number DRKS00025996.

## Introduction

Diabetes mellitus has increasingly become a widespread disease.^
1
^ As diabetes is a chronic disease, the term “cure” as a goal may not be
entirely accurate.^
2
^ As part of nonpharmacological interventions, individual self-management with
constant professional supervision is a necessity.^
3
^

Digital health applications (DHAs) have the potential to improve access to relevant
target groups, provide individualized feedback, and overall improve quality of care.^
4
^ However, patients cannot simply be expected to comply but should be provided
with products that promote compliance through ease of use and motivation for
incorporating self-management into daily life.^
5
^

The evidence on the effectiveness of DHAs for monitoring and self-management support
in patients with diabetes can be considered a weak and inconclusive.^6,7^ The inability to connect
devices from different manufacturers (eg, pen, glucometer, and app) creates an
evolving challenge for providers. This compromises the ability to appropriately
combine effective treatment options and complicates patients’ self-management.^
8
^

Despite these challenges for developers, health care professionals (HCPs), and patients,^
9
^ DHAs hold a great potential to improve diabetes self-management, largely due
to improved monitoring, immediate and ongoing feedback, and motivation.^7,10-13^

The aim of this study is to assess the effectiveness of a DHA on clinical outcomes in
patients with diabetes under real-life conditions. Collected data on blood values,
empowerment, self-management, mental health, and quality of life will provide the
necessary basis for certification of the investigated smartphone app as an official
DHA in Germany following the “DiGA Fast Track evaluation” as a guideline for the approval.^
14
^

## Methods

### Trial Design

A prospective, multicentric, randomized controlled trial (RCT) will be conducted
over a period of 6 months to investigate the effect of a DHA on HbA1c levels in
patients with type 1 and type 2 diabetes mellitus. To this end, we will compare
two groups of patients fulfilling the inclusion criteria (see Table 1): The control
group (CG) will only receive the standard diabetes care and the intervention
group (IG) will additionally use the DHA to monitor diabetes-relevant values
using various graphs and observe potential changes in these endpoints. Each
group will consist of at least 77 patients and will be supervised for a minimum
of 180 days. The schematic design of the DAVOS trial (E**V**aluation
**O**f the Impact of E**S**ysta on Hba1c in Patients with
Type 1 and Type 2 Diabetes mellitus in **DA**ily practice) is shown in
Figure 1.

**Table 1. table1-19322968221075333:** Inclusion and Exclusion Criteria in the DAVOS Trial.

*Inclusion criteria*
• Diabetes mellitus type 1 or 2 • ≥18 years old • Treated with insulin • HbA1c at baseline ≥7.5% and ≤11.0% • Not having used the investigated DHA in the past 12 months • Willing to use a smart glucometer and/or smart insulin pen • Internet access, smartphone/computer compatible with the DHA • Digital literacy to use a smartphone adequately
*Exclusion criteria*
• Using other apps linked to a BG meter or using an insulin pump or continuous glucose monitoring • Having used the investigated DHA in the past 12 months • <18 years old • Impairments (also mental impairments, eg, psychotic disorders) • Patients with home nursing (assisting BG testing) • Current participation in a weight loss program • Current participation in another study • Steroid therapy within the past three months (no exclusion criterion if used topically or inhaled less than five times a week) • Blood pressure ≥200 mm Hg at screening • BMI ≥40 kg/m² • Anemia (according to the WHO definition^ 15 ^) • GFR ≤40 mL/min • Current or planned pregnancy, breastfeeding women • Alcohol or drug abuse (within the past three months) • Employees of Emperra GmbH E-Health Technologies (or other institutions being involved in the trial)

Abbreviations: BG, blood glucose; BMI, body mass index; DHA, digital
health application; GFR, glomerular filtration rate; WHO, World
Health Organization.

**Figure 1. fig1-19322968221075333:**
[figure not shown]
Schematic design of the DAVOS trial (E**V**aluation
**O**f the Impact of E**S**ysta on Hba1c in
Patients with Type 1 and Type 2 Diabetes mellitus in **DA**ily
practice).

The decline of HbA1c value is the primary endpoint of the study. The values will
be monitored on three visits: in the beginning, after 90 days, and after 180
days. Furthermore, the IG will receive an additional telephone call seven days
after the first visit to resolve any technical barriers, including problems with
connected hardware (which participants will receive after Visit 1). All visits
are specified in Figure 2.

**Figure 2. fig2-19322968221075333:**
[figure not shown]
Visit schedule. Abbreviations: CG, control group; HCP, health care
professional; IG, intervention group.

The study as a prospective, multicentric, randomized, controlled trial was
approved by the German Federal Institute for Drugs and Medical Devices (BfArM)
on July 5, 2021, and will be submitted to the Independent Ethics Committee.

Five different study sites, guided by physicians with experience in digital
diabetes management (according to Good Clinical Practice [GCP]), are planned for
the execution of the study. Both physicians and practice staff are briefed to
collect the necessary values for the study. Patients will visit the office and
be treated by their physician as usual, except that they will be attending the
trial visits in addition.

### Participants

#### Eligibility criteria

Included in the trial are insulin-treated diabetes patients, who have agreed
to the conditions of the study. All patients should be willing to improve
self-management. Main prerequisite for participation is diabetes mellitus
(type 1 or 2) treated with insulin. Previous duration of diabetes and
insulin treatment are irrelevant. Patients, who do not use insulin yet
but—according to HCP—can profit from insulin therapy, can also be included
in the trial. Diabetes control is not important for inclusion as long as the
HbA1c value is ≥7.5% and ≤11.0%.

For all inclusion/exclusion criteria, see Table 1.

#### Recruitment and randomization

Recruitment of the patients will take place in routine clinical practice in
several medical practices/study centers in Germany.

A simple randomization will be performed with the generation of a
randomization list.^
16
^ For this purpose, participating physicians will perform individual
randomization by screening potential participants for their inclusion
criteria by study personnel. After signing the informed consent form and the
anamnesis questionnaire, patients then will be randomized using the
predesigned randomization list.

Patients who meet all inclusion criteria will then receive an invitation to
the first visit by post. Later, participants of the IG will be asked to sign
another consent form to use the DHA.

As this is not a blinded study, the results of randomization cannot be hidden
from the study centers. The division into IG and CG will be obvious to staff
and participants.

Pseudonymization will be performed using a code that patients will receive
upon consenting to the study. The data will not be passed on to third
parties.

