## Discussion

The hypothesis to be investigated in this study is that the use of a DHA has a
greater impact on the treatment of diabetes and improving glycemic control than
standard therapy. For patients, this could mean a great relief in everyday life and
improved support in managing their disease.

It is theorized that the provided self-management support, increased motivation, and
structured monitoring will have a positive impact on HbA1c levels, frequency of
hypoglycemia and hyperglycemia, and mental health.

Through interoperable procedures, patients can be optimally supported during the
study. Including the HCP in the study is beneficial because patients get to know
about the intervention in their usual setting, that is, routine physician
consultation. This way, there is no additional burden of the study, which could skew
results, and in addition, HCPs also learn how to use the DHA system and integrate it
into their daily practice.^
5
^

With regard to the current study design, it should be noted that an unblinded RCT
design risks biasing the results by various factors. First, selection bias could
arise because recruitment is unblinded in physicians’ offices. Selection bias is
mitigated by randomization, but, for example, patients who are not very compliant
could already be rejected by the physician.^
40
^ To avoid this, HCPs and practice staff are briefed before recruitment and
will receive a checklist of inclusion criteria listed by importance.

As the CG is not allowed to use the DHA, these participants also denied its potential
benefits. This could lead to an ethical dilemma as a risk of unblinding.^41,42^ Recent
studies have uncovered the problem that complete blinding is not possible in studies
including a CG to test a digital application.^
43
^

To compensate for these disadvantages and to minimize the suspected bias, it is part
of the closure management to invite the CG to use the DHA after completion of the
study.

However, if there is an effect from the intervention on the behavior of the CG, this
would underestimate the effect of the DHA rather than overestimate a positive effect.^
44
^

The usefulness and perceived usability are particularly crucial for the acceptance of
the proposed digital application and to improve patient compliance.^
45
^ On this point, the difficulty of defining “digital literacy” (see inclusion
criteria of Table 1)
appears. Participants should have a basic knowledge of computers and smartphones,

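### Recruiting physicians randomise from a predesigned list with no concealment described and eligibility possibly settled after allocation; separately, simple randomisation of 154 does not guarantee 77 per group

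*Protocol article*

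**What the plan says.** Under Recruitment and randomization, the protocol article states: "A simple randomization will be performed with the generation of a" randomization list. It continues: "For this purpose, participating physicians will perform individual" randomization, by way of screening for the inclusion criteria. Consent comes before allocation: "After signing the informed consent form and the" anamnesis questionnaire, patients are randomised from the "predesigned randomization list". The next paragraph says that patients who meet all inclusion criteria are then invited to the first visit by post, and that intervention patients later sign a further consent to use the app. On blinding: "As this is not a blinded study, the results of randomization cannot be hidden" from the centres.

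The Discussion acknowledges that selection bias could "arise because recruitment is unblinded in physicians" offices. It says that this bias is "mitigated by randomization, but, for example, patients who are not very compliant" might be turned away by the physician. The measures it names are a staff briefing and a checklist of inclusion criteria.

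On size, Trial Design says that each "group will consist of at least 77 patients and will be supervised for a minimum" of 180 days. Sample size calculation gives 77 per group and 154 in total, with dropout included.

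**The concern.** Randomisation protects against selection only if whoever decides on a patient's entry does not know which arm comes next, and if entry is final before the arm is revealed. The article gives the randomising role to the people who recruit, and neither of the safeguards it names hides an assignment. Several criteria leave room for judgement: digital literacy, willingness to use smart devices, and, for patients not yet on insulin, the professional's view that insulin would help. If a physician knew the arm while such a criterion was still open, motivated or digitally able patients could end up unevenly distributed between the groups. Analysis cannot fully repair that, and the trial is meant to support certification of the app.

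The second matter is one of consistency. Simple randomisation fixes the probability of each arm and leaves the count to chance, so a minimum group size equal to half the total is not a property of the design.

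**Working it through.** **Part 1: who allocates, and when.** No arithmetic applies, so the statements are set side by side.

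1. Actor. The physicians are said to perform the randomisation. The sentence on the allocation step itself is passive and names no one.
2. Tool. The list is drawn up in advance. The article does not say who generates it, who holds it, or whether upcoming entries are hidden.
3. Order. Screening and consent come first, then randomisation, then the invitation to patients meeting all criteria.
4. Criteria. Table 1 requires an HbA1c at baseline of 7.5% to 11.0%, and excludes current pregnancy. Trial Design places the first HbA1c value at the first visit. Measures and Questionnaires places HbA1c and the pregnancy test at every visit.
5. Reading 3 and 4 together: if the qualifying HbA1c is the one from the first visit, eligibility is completed after the arm is known to site and patient. If a screening value is used, it is not. The article does not say which.
6. Predictability. A simple sequence cannot be predicted from past allocations, so the open-label design does not by itself reveal the next arm. The exposure would come from access to the list, or from eligibility decisions made after allocation.

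**Part 2: group size.**

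The plan's figure first. With effect size 0.6625, power 0.95 and alpha 0.05 (taken as two-sided, which reproduces the figure), a two-sample t-test needs 61 per group. With 20% dropout, 61 / 0.8 = 76.25, rounded up to 77, or 154 in total. The stated number is reproduced.

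Under simple 1:1 randomisation the size of one group is Binomial(154, 0.5).

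- Both groups reach 77 only at 77/77: C(154, 77) / 2^154 = 0.064. The chance that one group falls short is 1 − 0.064 = 0.936.
- The standard deviation is √(154 × 0.25) = 6.2, and 77 ± 1.96 × 6.2 gives about 65 to 89. The exact 95% range is also 65 to 89. The expected size of the smaller group is 72.1.
- Reaching 77 in both groups with 95% probability would take 180 patients. Recruiting until both reach 77 would take about 164 on average.

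What the imbalance costs:

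| Effect size | No dropout, 77/77 | No dropout, 65/89 | After 20% dropout, 62/62 | After 20% dropout, 52/71 |
|---|---|---|---|---|
| 0.6625 (stated) | 0.983 | 0.981 | 0.955 | 0.950 |
| 0.442 | 0.777 | 0.767 | 0.684 | 0.670 |

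The second row uses 0.4 / √((0.8² + 1.0²) / 2) = 0.4 / 0.9055 = 0.442, the effect size that the stated difference and standard deviations imply. Its mismatch with 0.6625 is a separate matter. At the stated effect size the loss is about 0.2 points without dropout and 0.6 after it; at 0.442 it is 1.0 and 1.4 points. The dropout columns differ by one patient in total through rounding. Put another way, a 65/89 split is worth 2 × 65 × 89 / 154 = 75.1 per group instead of 77.

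**The case against.** The strongest reply is that a condensed article commonly leaves custody and release of the list to the full protocol. A list made in advance is equally compatible with a telephone service or sealed envelopes. Consent precedes allocation. The sentence on the physicians' role is garbled and may partly describe screening. The Discussion's example, rejection of less compliant patients, concerns who enters the trial at all and is not an admission of steering into one arm.

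Much of this stands. A reader might infer that the physicians can foresee the next allocation, but the article does not say so, and simple randomisation gives no pattern to guess from. A reader might also put a figure on the bias, but the documents supply no basis for one. The invitation sentence may be loose narrative order. What remains is stated text: recruiters are named as randomisers, and the order as written allows eligibility to be completed after allocation. Consent before allocation limits the exposure without closing it.

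On group size, it would be too strong to say that the design cannot deliver 77 per group: an exact split is possible, and recruiting beyond 154 would reach it. Nor does chance imbalance bias the comparison. The absence of blocking or stratification by diabetes type is therefore not an error. Blocks also bring back some predictability in an open-label trial, and blocks of 4 within sites would not guarantee 77/77 either.

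**Conclusion.** The allocation procedure needs correcting as written. It gives the randomising step to the recruiting physicians, describes no concealment in an open-label trial, and places the invitation of patients meeting all criteria after randomisation. This is a weakness in the stated procedure; the documents do not show that the next allocation is visible or that selection would occur. The size of any bias is unknown. The conclusion assumes that the article's wording and order reflect what sites will do. If the full protocol already separates recruitment from allocation, correcting the article's account is enough.

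The group-size statement conflicts with the randomisation method: a 6.4% chance of meeting it with exactly 154 patients, assuming independent 1:1 allocation. The consequence is small, under 1 point of power at the plan's effect size for a split as uneven as 65/89. It calls for a change of wording only.

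**What to change.** 1. Take the allocation step away from the recruiting physicians. Have someone independent of the sites hold the list centrally, or use sequentially numbered opaque sealed envelopes. State who generates the list, who holds it, and how the next assignment is concealed.
2. Release each allocation only after consent is signed and all eligibility criteria are recorded as confirmed, including the qualifying HbA1c and the criteria that rest on judgement. Reorder the recruitment text to match, and say which HbA1c measurement decides eligibility.
3. Restate the group size in Trial Design as about 77 per group.

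Permuted blocks of varying size, stratified by diabetes type, are optional. If used, they should be held centrally.

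The cost is a protocol amendment, best made before the first enrolment, and the set-up of a simple release step. No additional patients are needed. If the full protocol already provides for items 1 and 2, only the wording has to change.

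### Randomisation is placed before Visit 1, so the HbA1c entry check and the baselines can fall after open allocation, and an app consent asked of one arm only adds a further risk of bias

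*Protocol article*

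**What the plan says.** Recruitment and randomization describes these steps, in this order:

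1. Physicians carry out "randomization by screening potential participants for their inclusion" criteria.
2. After informed consent and the "anamnesis questionnaire, patients then will be randomized using the" prepared list.
3. "Patients who meet all inclusion criteria will then receive an invitation to" Visit 1.
4. The sentence runs on: "the first visit by post. Later, participants of the IG will be asked to sign" a second form, for use of the app. No matching step is described for the control group.

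The same section says that the trial is not blinded and that both staff and participants will know the allocation.

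Other sections fix where the baseline lies. Under Trial Design, HbA1c will "be monitored on three visits: in the beginning, after 90 days, and after 180" days. Statistical Analyses takes Visit 1 as the baseline for Visits 2 and 3. Table 1 words the entry criterion as "HbA1c at baseline ≥7.5% and ≤11.0" percent, while the blood pressure exclusion in the same table refers to screening. Measures and Questionnaires has HbA1c measured at every visit in each site's local laboratory. Trial Design says that connected hardware reaches participants after Visit 1.

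**The concern.** Randomisation makes the arms comparable for everything settled before it. A selection step that comes later, run by people who know the arm, can act differently in the two arms. As written, three things can fall on the wrong side of allocation:

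- **Eligibility.** The invitation filter and the HbA1c criterion. HbA1c is also the primary endpoint, so selection here acts on the outcome directly.
- **Baselines.** The Visit 1 HbA1c and any questionnaires completed then. This matters little for a laboratory value. It matters more for self-reported measures behind H3 and H4, which patients may answer differently once they know their arm.
- **The app consent.** It is asked of one arm only and gives that arm an additional point at which patients can leave.

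The Discussion accepts that physicians may turn away less compliant patients and relies on randomisation to limit the resulting selection bias. That defence works only if the turning away happens before allocation. The trial is meant to support certification of the app, so the integrity of the comparison matters.

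**Working it through.** **Order of events.** Randomisation follows consent and the questionnaire, and the postal invitation to Visit 1 follows randomisation. Baseline HbA1c is a Visit 1 measurement. Baseline HbA1c therefore comes after randomisation if the text is followed literally.

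**Which criteria are affected.** Step 1 shows that some screening comes first. Blood pressure is judged at screening, so it is not part of this point. The HbA1c range is tied to baseline. Step 3 then mentions meeting all inclusion criteria a second time, after randomisation. A Visit 1 value outside 7.5% to 11.0% would thus come to light when the arm is known. The article does not say whether such a patient is removed.

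**Sample size, for reference.** From the stated effect size of 0.6625 and power of 0.95, with two-sided alpha 0.05 (sidedness is assumed), a two-sample t test needs 61 per arm. Allowing for 20% dropout, 61 / 0.80 = 76.25, so 77 per arm, as planned. Moving randomisation does not alter this.

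**Loss of power if intervention patients who decline were dropped.** Evaluable patients per arm: 77 × 0.80 = 61.6, about 62. The article gives no refusal rate, so the first column is an assumption.

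| Extra loss, intervention arm | Evaluable (intervention / control) | Power at 0.6625 |
|---|---|---|
| 0% | 62 / 62 | 0.955 |
| 5% | 59 / 62 | 0.951 |
| 10% | 55 / 62 | 0.944 |
| 20% | 49 / 62 | 0.930 |

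The loss is small, so the issue is bias. (Whether 0.6625 follows from the stated means and standard deviations is a separate matter.)

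**Bias if those patients were dropped.** Let r be the share dropped and D the amount by which their HbA1c change is worse than that of patients who sign, whose mean change is m. The full-arm mean is (1 − r)m + r(m + D) = m + rD. Analysing only those who sign shifts the arm mean by rD in favour of the app. Both r and D are assumptions.

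| r | D | rD (points) | Share of 0.3 | Share of 0.4 |
|---|---|---|---|---|
| 5% | 0.2 | 0.01 | 3% | 2.5% |
| 10% | 0.4 | 0.04 | 13% | 10% |
| 20% | 0.8 | 0.16 | 53% | 40% |

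Here 0.3 is the clinically meaningful difference in Table 2 and 0.4 is the reduction assumed under Sample size calculation.

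**If they are kept as allocated.** The formula above no longer applies. Suppose the app effect is 0.4 in those who sign and zero in those who do not. The expected difference is then (1 − r) × 0.4, which is 0.38 at r = 5% and 0.32 at r = 20%. The effect is diluted and the app is not favoured.

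No figure can be put on differential use of the inclusion check. The article gives neither the number of patients whose HbA1c might fall outside the range at Visit 1 nor the interval between randomisation and Visit 1.

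**The case against.** The strongest reply is that this is a condensed article and that little of the harm is stated in it.

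- **Exclusion after refusal.** A reader might infer that intervention patients who do not sign leave the trial. The text does not support this. They are asked to sign a consent for app use, and nothing removes those who decline from follow-up or analysis. The analysis population is commonly left to the full protocol or analysis plan. Jump-to-reference imputation, which the article names, is usually a conservative choice for missing data in the active arm. This stands, and it limits the consent point to a risk.
- **Eligibility decided wholly after allocation.** A reader might infer this too. It goes too far: screening is described first, the first questionnaire covers inclusion criteria, and practice files may already hold an HbA1c value. Repeating a test at every visit does not show that first eligibility is decided at Visit 1. What remains is the HbA1c criterion tied to baseline and the second inclusion filter after randomisation.
- **Unwilling patients are screened out early.** Table 1 requires willingness to use a smart glucometer and/or pen in both arms. This probably lowers refusal, but it is not consent to the app.
- **Late baselines do little harm.** HbA1c is a laboratory value, a file value may replace a missing one, and the article does not say exactly when patients learn their arm. This is fair for HbA1c and weaker for questionnaires, where the direction of any shift is unknown.
- **The figures may settle the order.** The schema and the visit schedule are not reproduced in the text reviewed. Even if they show a sound order, the recruitment text would need to agree with them.

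**Conclusion.** The point holds as a weakness in the written order of procedures. Randomisation comes before the invitation to Visit 1, the invitation is limited to patients who meet the inclusion criteria, and baseline HbA1c is taken at Visit 1 in an open trial. Following that text allows the HbA1c criterion and the inclusion check to be applied with the arm known, and places Visit 1 baselines after allocation.

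The app consent in the intervention arm adds a possible arm-specific exit. It is not a demonstrated exclusion. The range of 0.01 to 0.16 points depends on an assumed refusal rate, an assumed difference in HbA1c course, and patients who decline being left out of the analysis. If they are kept, the consent leads to non-adherence and dilution. The true size is unknown.

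This is more than a request for detail, because the order can be changed before enrolment and cannot be repaired afterwards.

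**What to change.** Rewrite Recruitment and randomization so that:

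1. All patients sign trial consent and a conditional consent to use the app if allocated to it.
2. All entry criteria, including the HbA1c range, are confirmed, and baseline HbA1c and questionnaires are completed at Visit 1.
3. Randomisation takes place only after that.
4. The separate consent for the intervention group after allocation is dropped.
5. Intervention patients who never use the app stay in follow-up and in the primary analysis in their allocated arm.

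The visit schedule should show the same order. The cost is an amendment to the protocol and consent form. It is cheap at this stage: Trial Design describes ethics submission as still to come and has hardware provided after Visit 1 in any case. The downside is that allocation waits for the Visit 1 laboratory result and introduction to the app follows it. Sample size is unchanged.
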